#### Feasibility

More than 2500 fusion biopsies are performed annually across participating centers. Recruitment expectations: 1908 within 36 months (636/year; ~64 per center/year; 51 analyzable). PRIMA recruitment does not depend solely on community referrals but is expected to be supported due to advantages for patients such as cost-covered mpMRI and biopsy avoidance in negative imaging cases.

### Recruitment {15}

Eight established centers perform > 2500 fusion biopsies annually, providing sufficient recruiting capacity. Stopping rules are applied if < 50% first-year enrollment or < 70% by year two.

## Assignment of interventions: allocation

### Sequence generation {16a}

Participants will be randomized in a 1:1 allocation ratio to either Arm A (targeted biopsy only) or Arm B (targeted + systematic biopsy). Randomization will use computer-generated permuted blocks of variable size and will be stratified by study center to ensure balance across recruitment sites.

### Concealment mechanism {16b}

Allocation concealment will be ensured through a secure web-based automated randomization system integrated with the electronic data capture software. The system will release the assignment only after participant eligibility is confirmed, preventing foreknowledge or prediction of allocation. Treating investigators and study personnel remain blinded to allocation until the moment it is irreversibly generated.

### Implementation {16c}

Randomization will be initiated by authorized study personnel at each participating study site via the secure randomization portal. Assignment to either intervention arm will then be automatically recorded within the trial documentation system. The coordinating investigator and monitoring team will not have access to the sequence generation algorithm or block sizes.

## Assignment of interventions: blinding

### Who will be blinded {17a}

Clinical teams cannot be blinded due to procedural differences between study arms. Radiological assessment (including PI-RADS scoring) is performed prior to randomization and is therefore inherently blinded to treatment allocation. Biostatistical analyses will be conducted on pseudonymized datasets, with treatment allocation unmasked only after database lock, following finalization of the statistical analysis plan.

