#### MR in-bore biopsy

For participants with PI-RADS 4–5 lesions and negative TB or TB + SB, MR in-bore biopsy will be offered after consensus reading. Needle placement will be confirmed in two imaging planes, and 2–4 cores per lesion will be acquired, with additional cores permitted if targeting is inaccurate.

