#### Secondary outcomes

Patient-reported outcomes (EPIC-26, EORTC-QLQ-C30, VAS)

Measured using validated questionnaires (metric: continuous scores), analyzed as mean changes over time and between groups (aggregation: mean differences), assessed at baseline, 30 days, and 12 months.Biopsy-related complications

Defined as adverse events within 30 days post-biopsy (measure: clinical assessment; metric: categorical/binary), summarized as proportions by study arm, assessed at 30 days post-procedure.Biopsy avoidance due to mpMRI triage

Defined as the proportion of participants not undergoing biopsy due to non-suspicious mpMRI findings (PI-RADS 1–2 or PI-RADS 3 with PSAD ≤ 0.15), reported as proportion, assessed at screening.Diagnostic performance of DRE

Defined as the association between DRE findings and biopsy outcomes (metric: sensitivity, specificity), analyzed cross-sectionally at baseline and biopsy.Biopsy approach (transrectal vs. transperineal)

Compared in terms of pain (VAS score) and infection rates (binary), summarized as mean differences and proportions, assessed within 30 days post-biopsy.MR in-bore biopsy yield

Defined as detection of csPCa in participants undergoing MR in-bore biopsy after negative or ISUP 1 results (metric: binary), reported as proportion, assessed within 3 months post-biopsy.Detection of higher-grade cancer (ISUP ≥ 3)

Defined as presence of ISUP ≥ 3 cancer on histopathology (metric: binary), reported as proportion, assessed at index biopsy.Comparison of bpMRI vs mpMRI

Retrospective comparison of detection performance (metric: paired binary outcomes), analyzed using constrained maximum likelihood methods, assessed at baseline imaging.Change in PI-RADS score

Defined as change in PI-RADS category between baseline and follow-up MRI (metric: ordinal change), reported as proportions of up- or downgrading, assessed at 12 months.Index-lesion-only analysis

Detection of csPCa based on index lesion targeting only (metric: binary), reported as proportion, assessed at index biopsy.AI and radiomics validation

Diagnostic performance of AI-based models (metric: AUC, sensitivity, specificity), analyzed retrospectively, assessed using baseline imaging and biopsy outcomes.

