### Plans to promote participant retention and complete follow-up {18b}

Participant retention in PRIMA is supported by clear communication of the clinical relevance of structured imaging follow-up and by scheduling support from study nurses at each site. Reminder systems, including scheduled telephone, electronic or postal notifications, will be used to encourage attendance at follow-up visits, particularly the 30-day safety visit and the 12-month mpMRI assessment. Missed appointments will be actively followed up by site investigators or study nurses to re-schedule assessments where feasible.

If participants discontinue allocated biopsy procedures, routinely collected clinical data—including follow-up MRI results, histopathology reports, adverse events and patient-reported outcomes—will continue to be collected unless consent is formally withdrawn. Reasons for withdrawal or protocol deviation will be documented in the electronic trial database.

For participants lost to follow-up, electronic hospital records may be reviewed to identify biopsy results, MRI findings, or cancer diagnoses when permitted by local data-protection regulations. Participants diagnosed with csPCa (ISUP ≥ 2) will exit the trial and enter guideline-based standard-of-care treatment; data collection until the time of exit remains part of the primary analysis.

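### Radiology is called inherently blinded because it precedes randomisation, but the 12-month PI-RADS score and the consensus reading before in-bore biopsy come after it and no masking is stated for either

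*Protocol article*

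**What the plan says.** Section {17a} makes two statements that bear on image reading. On site staff: "Clinical teams cannot be blinded due to procedural differences between study arms". On radiology: "Radiological assessment (including PI-RADS scoring) is performed prior to randomization and is therefore inherently blinded to treatment allocation". The second sentence is not limited to a visit or a scan, and it names PI-RADS scoring explicitly. Section {17b} adds that neither participants nor treating clinicians are blinded.

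Elsewhere the article schedules further image reading:

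- **12-month score.** A secondary outcome in section {12} is "change in PI-RADS category between baseline and follow-up MRI (metric: ordinal change), reported as proportions of up- or downgrading, assessed at 12 months". The retention section {18b} names the visit at which it is obtained: "particularly the 30-day safety visit and the 12-month mpMRI assessment". Section {20b} uses the same result (stable versus up- or downgraded) as a subgroup for the effect of arm on csPCa detection.
- **Consensus reading.** For PI-RADS 4–5 lesions with a negative allocated biopsy, section {11a} says "MR in-bore biopsy will be offered after consensus reading". In-bore yield is a secondary outcome in section {12}.
- **bpMRI versus mpMRI.** Section {12} describes a "Retrospective comparison of detection performance (metric: paired binary outcomes"), on baseline imaging. It does not say when, or by whom, a bpMRI reading is made.

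**The concern.** The sentence presents masking as a consequence of timing. Where the timing does not hold, the masking does not follow, and because the section treats radiology as settled it offers no other protection for the later readings.

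PI-RADS is a judged ordinal score. A reader who knows that an Arm A man had no systematic cores may be slower to downgrade a lesion than one who knows that an Arm B man also had 12 negative systematic cores. A difference between arms in PI-RADS stability, in-bore use or in-bore yield could then reflect what the reader knew rather than disease. This matters for interpretation. Section {11c} relies on follow-up imaging and in-bore biopsy as the safeguard against missed csPCa in both arms, and the Discussion makes the role of in-bore biopsy in a targeted-only strategy an explicit aim.

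**Working it through.** The article states no figure on this point, so the main check is one of timing: each reading is placed before or after randomisation and compared with section {17a}.

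| Reading | Where described | Timing | Does the {17a} sentence hold? |
|---|---|---|---|
| Baseline mpMRI deciding eligibility | {11a}, {13}, {16b} | Before: "The system will release the assignment only after participant eligibility is confirmed" | Yes |
| Consensus reading before in-bore biopsy | {11a} | After randomisation and after a negative TB or TB + SB | No |
| 12-month PI-RADS score | {12}, {18b}, {20b} | About a year after the allocated biopsy | No |
| bpMRI reading | {12} | Baseline images; time of reading not stated | Cannot be determined |
| Co-primary endpoints | {12} | Index-biopsy histopathology, not an image reading | Not concerned |

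The abstract confines in-bore biopsy to persistent PI-RADS 4–5 lesions, which suggests that lesion status is judged again after the biopsy.

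**How many men could be affected (illustrative only).** Inputs from section {14}: 477 analysable men per arm; csPCa 50% in Arm B and, with the assumed difference of −5%, 45% in Arm A; ISUP 1 15% in Arm B and 15% × 0.6 = 9% in Arm A; PI-RADS 4–5 in 50 of every 60 randomised men.

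- *12-month score.* Men without csPCa at index biopsy: 477 × 0.55 + 477 × 0.50 = 262 + 239 = 501, out of 2 × 477 = 954. This is a ceiling: repeat MRI depends on biopsy results {13}, and men found to have csPCa at in-bore biopsy leave the trial {18b}.
- *Consensus reading.* No cancer at index biopsy: 1 − 0.45 − 0.09 = 46% in Arm A and 1 − 0.50 − 0.15 = 35% in Arm B. If PI-RADS 3 and PI-RADS 4–5 men were negative equally often (assumed), the counts are 477 × 0.46 × 50/60 = 183 and 477 × 0.35 × 50/60 = 139.
- *Sensitivity to that assumption.* PI-RADS 3 men number 477 × 10/60 = 79.5 per arm. If 70% of them were negative (assumed), 79.5 × 0.70 = 55.7 negatives would be PI-RADS 3, leaving 219.4 − 55.7 = 164 in Arm A and 167.0 − 55.7 = 111 in Arm B.
- *Who is counted.* These counts use negative biopsies only, as in {11a}. The in-bore yield outcome in {12} also admits men with ISUP 1, which would raise them.

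The article gives nothing on how often knowledge of the arm would change a reading, so no number of altered decisions is calculated.

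**The case against.** The strongest reply is that context narrows the sentence: the radiological assessment that precedes randomisation is plainly the baseline mpMRI, and instructions for later readers belong in the quality and operations handbooks to which a condensed article refers. The second half has force, since missing reader instructions alone would be no finding. The first half does not rescue the wording. The sentence is unqualified, it names PI-RADS scoring, and PI-RADS scoring recurs at 12 months as an outcome. The article states a safeguard that cannot exist for those readings.

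The other objections set limits, and they stand:

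- A reader might infer that later readers are known to be unblinded. The article says this of clinical teams, participants and treating clinicians, not of radiologists. What can be said is that nothing stated prevents it.
- A reader might infer that all three later comparisons are read after randomisation. For bpMRI this is not established: the reading time is not given, and the reading could be derived from the baseline sequences or scores. The comparison is also paired within patient, so knowledge of histology matters more there than knowledge of the arm.
- A reader might infer that the main result is at risk. It is not.
- Neither definition, PI-RADS change nor in-bore yield, specifies a between-arm test. Section {20a} treats secondary outcomes descriptively, with inference where appropriate, and the follow-up imaging subgroup is exploratory.
- Withholding systematic-biopsy results from the consensus readers would restrict the information used for a decision on a further biopsy. That is clinical management and is not proposed.

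**Conclusion.** The blinding statement is wrong for two readings, the 12-month PI-RADS score and the consensus reading before in-bore biopsy. This follows from the article's own schedule and needs no numerical assumption. The consequence is confined to secondary and exploratory results: PI-RADS change, the subgroup built on it, and in-bore use and yield. These are open to arm-dependent reading; that such reading will occur is not shown. The co-primary endpoints are untouched.

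The counts serve only as scale. About 501 is a ceiling on 12-month scores among analysable randomised men. The figures of 183 and 139 reaching the consensus reading depend on equal negativity across PI-RADS categories and on counting negative biopsies only; they fall if PI-RADS 4–5 men are more often positive. The size of any bias cannot be estimated from the documents.

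**What to change.** 1. In {17a}, limit the sentence to the baseline mpMRI that determines eligibility.
2. State that the existing readers enter and lock the 12-month PI-RADS score before arm and systematic-biopsy results are disclosed to them. Once it is locked, all information is available for care as usual.
3. Do not describe the consensus reading as blinded. State its actual masking status, leave open what may inform the biopsy decision, and report in-bore use and yield with that status made plain.
4. If the retrospective bpMRI comparison involves re-reading images, state that those readings are made without knowledge of histology and of the DCE series.

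The cost is protocol wording and an entry step that locks the 12-month score. No extra readers, patients or visits are needed. The one practical burden is that sites must withhold arm and systematic-biopsy results from the reader until that score is entered. There is time: the Trial status section reports no enrolment at manuscript submission and a planned start of 15 April 2026, so on that schedule 12-month readings would not fall due before about April 2027.

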### Procedure for unblinding if needed {17b}

Not applicable, as no blinding of participants or treating clinicians is implemented; therefore, no unblinding procedures are required.

## Data collection and management

### Plans for assessment and collection of outcomes {18a}

Outcome, baseline, and follow-up data will be collected using standardized electronic case report forms (eCRFs) implemented in a centralized, web-based clinical data management platform hosted by the German Cancer Research Center (DKFZ), Heidelberg. Data collection is performed by trained study personnel at participating sites following a standardized operations manual and quality assurance procedures.

Clinical, imaging, procedural, and pathological outcome data will be documented based on predefined categories and automated plausibility and range checks to ensure accuracy and completeness. Patient-reported outcome measures (PROMs) will be collected using validated German language versions of standardized instruments, including EPIC-26, EORTC-QLQ-C30 and VAS scales. Questionnaires will be completed on paper or electronically and transferred to eCRFs using double-check verification if manually entered. Radiological findings will be reported according to PI-RADS v2.1, and MR image quality will be rated using PI-QUAL v2. All pathologic assessments follow ISUP 2014 Gleason grading criteria. Detailed eCRF structures and data collection forms are available in the study operations handbook.

### Plans to promote participant retention and complete follow-up {18b}

Participant retention in PRIMA is supported by clear communication of the clinical relevance of structured imaging follow-up and by scheduling support from study nurses at each site. Reminder systems, including scheduled telephone, electronic or postal notifications, will be used to encourage attendance at follow-up visits, particularly the 30-day safety visit and the 12-month mpMRI assessment. Missed appointments will be actively followed up by site investigators or study nurses to re-schedule assessments where feasible.

If participants discontinue allocated biopsy procedures, routinely collected clinical data—including follow-up MRI results, histopathology reports, adverse events and patient-reported outcomes—will continue to be collected unless consent is formally withdrawn. Reasons for withdrawal or protocol deviation will be documented in the electronic trial database.

For participants lost to follow-up, electronic hospital records may be reviewed to identify biopsy results, MRI findings, or cancer diagnoses when permitted by local data-protection regulations. Participants diagnosed with csPCa (ISUP ≥ 2) will exit the trial and enter guideline-based standard-of-care treatment; data collection until the time of exit remains part of the primary analysis.

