#### Sample size

The sample size is derived from the following expected PI-RADS distribution (own institutional data and PRECISION trial data [8, 23]): 25% PI-RADS 1–2, 25% PI-RADS 3 (15% PSAD ≤ 0.15 and 10% PSAD > 0.15), 30% PI-RADS 4, and 20% PI-RADS 5. Thus, the prevalence of PI-RADS 4/5 and PI-RADS 3 PSAD > 0.15 is estimated at 60%. The estimated prevalence of csPCa in this cohort is 50%, and the detection of low-grade PCa (ISUP 1) is expected to be 15%.

Based on prior evidence, targeted biopsy alone is expected to reduce ISUP 1 detection by at least 40% [7], and SB adds approximately 5% absolute incremental csPCa detection according to randomized trials and a Cochrane meta-analysis [9, 10, 13, 14]. Non-inferiority of TB alone compared with TB + SB will be evaluated by testing H0: Δ0 = πTB − πSB + TB ≤ − δNI, with a non-inferiority margin of δNI = 13%. The non-inferiority margin of 13% was chosen based on prior evidence demonstrating an approximate 4–5% incremental detection of clinically significant prostate cancer with systematic biopsy, allowing for a conservative margin that maintains clinical relevance. Assuming πSB + TB = 50% and a true difference of Δ = − 5%, 477 patients per arm ensure 80% power at one-sided α = 0.05.

Superiority in avoiding ISUP 1 diagnoses will be tested under H0: πTB/πSB + TB ≥ 1. With πSB + TB = 15% and a true reduction ratio to 60%, a sample size of 460 patients per arm ensures 88% power at *α* = 0.05.

Therefore, 1590 analyzable patients are required (2 × 477/0.6 = 1590), and accounting for 20% dropout, approximately 1908 must be allocated within 3 years.

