## Statistical methods

### Statistical methods for primary and secondary outcomes {20a}

The primary analysis will compare the detection proportion of clinically significant prostate cancer (csPCa; ISUP ≥ 2) between Arm A (TB only) and Arm B (TB + SB) using a non-inferiority framework. Non-inferiority for csPCa detection will be assessed based on the absolute difference in detection proportions (π_TB − π_TB + SB), evaluated using the likelihood score test by Gart and Nam for binomial parameters at a one-sided α level of 0.05. The non-inferiority margin is δ = 13%. Superiority testing for the secondary co-primary endpoint (detection of clinically insignificant PCa, ISUP 1) will be evaluated based on the ratio of detection proportions (π_TB/π_TB + SB) using a one-sided α level of 0.05. All hypothesis tests apply a fixed global significance level of *α* = 0.05.

Secondary outcomes—including biopsy-related complications, biopsy avoidance, diagnostic performance measures, and biopsy approach comparisons—are defined in the Outcomes section according to domain, measurement, metric, method of aggregation, and timepoint. Biopsy-related complications will be summarized as proportions by study arm at 30 days post-procedure. Biopsy avoidance will be reported as the proportion of participants not undergoing biopsy following mpMRI triage at screening. Diagnostic performance outcomes (e.g., DRE, bpMRI vs mpMRI) will be evaluated using standard accuracy measures (e.g., sensitivity, specificity) where applicable.

All detection outcomes are defined as proportions (number of participants with the outcome divided by the number of participants undergoing biopsy in the respective arm). Secondary outcomes will be analyzed descriptively and, where appropriate, using inferential statistical methods.

Patient-reported outcomes (EPIC-26, EORTC-QLQ-C30, VAS) will be analyzed using mixed models for repeated measures (MMRM), including treatment arm, timepoint, and baseline values as covariates.

A detailed statistical analysis plan (SAP) will be finalized and archived prior to database lock and prior to any unblinded analyses.

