### Adverse event reporting and harms {22}

Adverse events (AEs) and serious adverse events (SAEs) related to biopsy procedures will be collected systematically from the time of intervention up to 30 days post-biopsy and documented in the electronic case report forms. In addition, specific complications will be actively assessed at 30 days using a structured patient survey, including sepsis, hospitalization, bleeding, urinary retention, persistent pain, hemospermia, and urinary tract infection.

SAEs will be reported to the sponsor and relevant ethics committees in accordance with national regulatory requirements. All events will be reviewed by the coordinating investigators.

In publications, all collected adverse events will be reported descriptively by study arm, including frequencies and severity grading. Serious adverse events and clinically relevant complications will be reported in detail to ensure transparent and comprehensive safety reporting.

The frequency and nature of biopsy-related complications are predefined secondary outcomes.

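### Men found to have csPCa leave the trial, so the planned 12-month patient-reported comparison lacks nearly half the randomized men and is not a randomized comparison

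*Protocol article*

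**What the plan says.** Four parts of the Protocol article bear on this.

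- **Retention {18b}.** Men with csPCa "will exit the trial and enter guideline-based standard-of-care treatment", and "data collection until the time of exit remains part of the primary analysis". No date is given for the exit relative to the histology report or the 30-day visit. The preceding paragraph promises continued collection of adverse events and patient-reported outcomes, but for another group: "If participants discontinue allocated biopsy procedures, routinely collected clinical data" continue to be gathered unless consent is withdrawn.
- **Outcomes {12}.** EPIC-26, EORTC-QLQ-C30 and VAS are secondary outcomes compared between groups, "assessed at baseline, 30 days, and 12 months". Nothing restricts them to men without csPCa. Complications are "Defined as adverse events within 30 days post-biopsy".
- **Statistical methods {20a}.** The scores "will be analyzed using mixed models for repeated measures (MMRM"), with arm, timepoint and baseline value as the listed terms.
- **Adverse events {22}.** Events are collected up to 30 days after biopsy, and "specific complications will be actively assessed at 30 days using a structured patient survey". No group is exempted.

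**The concern.** A man who refuses his allocated biopsy is followed for questionnaires. A man who is biopsied as allocated and found to have csPCa is not, as the text reads. The second group is about half of those randomized.

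The loss is not haphazard. The event that removes a man is a co-primary endpoint, and the trial assumes that the allocated procedure changes how often it occurs. Comparing the remaining men at 12 months therefore conditions on an event after randomization that depends on arm. The men who leave are also those who go on to cancer care, and the Background section itself names treatment side effects and psychological burden as consequences of diagnosis and treatment.

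Patient-reported outcomes are the burden side of the argument for omitting systematic biopsy, and the Background section presents them as essential. If the 12-month result is reported as a randomized arm comparison, readers will give it more weight than it can bear.

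**Working it through.** **Inputs, all from Sample size {14} unless stated**

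- csPCa rate with TB + SB: "The estimated prevalence of csPCa in this cohort is 50" per cent, used there as the Arm B detection rate.
- Assumed true difference: −5 points, so 45% in Arm A.
- Margin: 13 points. One-sided α = 0.05, power 80%, 477 analyzable men per arm (954 in total).

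**Step 1. Reproduce the plan's figure.** With unpooled variance,

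n = (1.645 + 0.842)² × (0.45 × 0.55 + 0.50 × 0.50) / (0.13 − 0.05)² = 6.18 × 0.4975 / 0.0064 ≈ 481 per arm.

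A score-type calculation with the variance constrained under the null gives 80.07% power at n = 477. The stated 477 is reproduced, so 45% and 50% are the rates on which the plan rests.

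**Step 2. Count the exits at index biopsy.** Exits per arm = 477 × csPCa rate.

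| TB rate (A) | TB + SB rate (B) | Exits A | Exits B | Share of 954 | Left A / B |
|---|---|---|---|---|---|
| 45% (plan) | 50% | 214.65 | 238.5 | 453.15 (47.5%) | 262.35 / 238.5 |
| 50% (no difference) | 50% | 238.5 | 238.5 | 477 (50%) | 238.5 / 238.5 |
| 37% (at the margin) | 50% | 176.49 | 238.5 | 414.99 (43.5%) | 300.51 / 238.5 |

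csPCa found later at MR in-bore biopsy would add exits. Its rate is not given.

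**Step 3. Who is left.** Assume equal underlying prevalence in the two arms, and that TB + SB finds whatever TB alone would find plus 5 points. The men left are then 55% of Arm A and 50% of Arm B. In Arm A, 0.05 / 0.55 = 9.1% of those left have csPCa that TB + SB would have found. Their counterparts in Arm B have gone.

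**Step 4. What that mix alone could do (illustration only).** If those men differ from the other men left by d standard deviations at 12 months, the arm difference shifts by d × 0.0909: 0.018 SD for d = 0.2, 0.045 SD for d = 0.5 and 0.09 SD for d = 1. The document gives no value or sign for d. This also leaves out the larger question of how the men who exited would have scored.

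**Step 5. Precision (illustrative: 80% power, two-sided 0.05).** Detectable difference = 2.80 × √(1/nA + 1/nB). With all 954 men it is 2.80 × √(2/477) = 0.18 SD. With those left it is 2.80 × √(1/262.35 + 1/238.5) = 0.25 SD.

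**Step 6. What the model can do.** Under missing at random, the MMRM predicts 12-month scores for exited men from men in the same arm with similar observed scores. Those men have no detected csPCa. Adding the biopsy result as a covariate would not solve this, because no man with csPCa at index biopsy would have a 12-month score from which to learn.

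**Step 7. Day 30, sections side by side.** If exit occurs at the histology report, and that comes before day 30, the retention section and the adverse-event section conflict for about half of biopsied men. If exit follows the 30-day visit, they agree and only later data are lost. The text does not say which applies.

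**The case against.** The strongest reply concerns scope. A reader might infer from the exit rule that 30-day complications and questionnaires are lost for half the men. The document does not support that. The adverse-event section collects events and a survey to day 30 without exemption, the complication outcome covers the same window, the retention section itself promotes attendance at the 30-day safety visit, and the exit is undated. The article is also condensed: the schedule figure is not shown, and an operations handbook is cited for data collection forms. This stands. At day 30 there is a possible conflict to reconcile, and no demonstrated loss.

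It can also be said that both co-primary endpoints are read at index biopsy, before any exit. No sample size, test or primary conclusion changes. This stands too.

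A third reply is that 12-month scores in treated men mostly reflect treatment, so not following them is defensible; that exit rates are expected to differ by only 5 points; and that day-30 scores, if kept, inform the MMRM. In part this stands: the bias may be small, and restricting follow-up is a legitimate choice. But Outcomes {12} and Statistical methods {20a} state a between-arm comparison to 12 months with no such restriction. Day-30 scores cannot carry information on what happens after treatment starts. The missing-data section {20c} offers complete-case and worst-case analyses for key endpoints. A complete-case analysis uses exactly the selected men, and the section does not say whether patient-reported outcomes count as key.

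**Conclusion.** The concern holds for the 12-month patient-reported outcomes. On the plan's rates about 453 of 954 men (47.5%; 43.5% to 50% for TB rates from 37% to 50%) would have no 12-month scores, leaving about 262 against 239. Because the exit depends on a co-primary endpoint that the allocated biopsy helps to determine, the 12-month contrast is not a randomized comparison, and missing at random is doubtful for men who leave to be treated. This rests on reading the exit as the end of questionnaire collection. The text supports that reading, since only data up to exit are kept and the continued-collection provision names another group.

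The size and direction of the bias cannot be computed from the document. The 30-day question is limited to two sections that must be reconciled. Because only secondary outcomes are touched, this does not threaten the trial's main conclusion and ranks below a mandatory correction. It is still best settled before enrolment, since an analysis plan cannot recover questionnaires that were never sent.

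**What to change.** - **Retention {18b}.** Reword so that a csPCa diagnosis ends only study imaging and in-bore follow-up, and extend the continued-collection sentence to these men.
- **Day 30.** State in {18b} and {22} that adverse-event collection, the structured survey and the 30-day questionnaires apply to every biopsied man, whatever the histology.
- **12 months.** Choose one of two courses and say so in {12} and {20a}: keep sending the existing questionnaires to men with csPCa, so that all randomized men can be compared; or report 12-month scores descriptively in men without detected csPCa, and not as a randomized arm comparison.

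The change concerns data collection only and leaves clinical care as it is. The cost is existing questionnaires for about 450 more men, plus consent and protocol wording. The second 12-month option avoids most of that cost but gives up the 12-month arm comparison. The article reports that no participants had been enrolled at submission, which is the cheapest time to make the change.
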